### Sample size {14}

The sample size was calculated for the primary objective (treatment effect up to 9 months postoperatively) based on the Hotelling-Lawley trace [24, 25]. Based on a standard deviation of 15 [23], correlation of the repeated measures of 0.7 (data from our phase I trial [21]), and with a power of 0.8 and alpha of 0.05, a minimum of 44 patients should be included to detect a minimal clinical relevant treatment effect of 10 for KOOS [23]. To account for potential loss to follow-up, and uncertainties in the correlation pattern and standard deviation for nonsurgical treatment, this was rounded up to 60 patients in total.

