## Statistical methods

### Statistical methods for primary and secondary outcomes {20a}

Data will be analyzed using IBM SPSS (version 15.0.0.2, Chicago, IL). Data from the primary objective (KOOS, EQ-5D-5L) will be presented as continuous variables. To compare between the two treatment groups, a mixed model analysis will be performed, with treatment group and assessment date of the PROMs (e.g., baseline, 3 months, 6 months) as fixed factors. Differences will be considered statistically significant for the fixed effect of treatment groups if *p* < 0.05 [30]. The 95% confidence interval of the fixed effect size will be used to assess whether treatment difference reaches the minimally clinical important difference.

T1rho-scores will be calculated from the biochemical MRI scans; differences in T1rho-scores will be compared between the time points *t* = 0 (at inclusion before IMPACT or nonsurgical treatment) and *t* = 6 and 18 months after inclusion or surgery. Differences will be compared using Student’s *t* test. The differences in T1rho-score will be tested for normality using Q–Q plots. *P* values less than 0.05 will be considered significant. We will calculate the ICERs of IMPACT vs. nonsurgical treatment and vs. delayed surgical treatment in terms of cost/QALY over a 5-year time horizon. The effect of uncertainty in input parameters on the ICERs will be calculated by means of one-way sensitivity analysis as well as probabilistic sensitivity analyses using Monte Carlo simulation.

All (S)AE(I)s will be summarized and recorded including the nature, date and time of onset, date of resolution, determination of seriousness, severity, action taken, outcome, and possible causality to study treatment. SAE data will be presented in a descriptive manner.

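### The 44 patients for 80% power match a group-by-time interaction, not the treatment main effect declared as the primary test; under that test the margin from 44 to 60 is used up

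*Protocol article*

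**What the plan says.** Sample size {14} of the protocol article gives these inputs: "Based on a standard deviation of 15", "correlation of the repeated measures of 0.7", "with a power of 0.8 and alpha of 0.05". The calculation is "based on the Hotelling-Lawley trace", and the result is that "a minimum of 44 patients should be included to detect a minimal clinical relevant treatment effect of 10 for KOOS". This is raised to 60 to cover loss to follow-up and uncertainty about the correlation pattern and the control-arm SD. The section does not say which hypothesis was powered or how the 10-point effect runs over the visits.

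Statistical methods {20a} declares a mixed model with two fixed factors, treatment group and assessment date. Baseline is given as one of the example dates. The decision rule is: "Differences will be considered statistically significant for the fixed effect of treatment groups", at p < 0.05. The 95% confidence interval of the same fixed effect is to be compared with the minimal clinically important difference. The section names neither a treatment-by-time interaction nor a baseline covariate.

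Objectives {7} sets the primary comparison at 3, 6 and 9 months, and Outcomes {12} takes it up to 9 months after randomization.

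**The concern.** A power figure belongs to one hypothesis. With repeated measures, the Hotelling-Lawley trace can test an interaction, a main effect or a joint difference, and these need very different numbers of patients under the same SD and correlation. A high correlation helps a test that uses within-patient change. It hurts a main effect that averages the visits, because the average is then little more precise than a single visit.

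If 44 comes from one hypothesis and the trial is decided on another, the stated 80% does not apply and the 16 patients added as a margin may not be one. A second consequence concerns estimation. When baseline counts as an outcome visit, randomization makes its expected difference zero, so the fixed effect averages that zero in. The confidence interval set against the clinically important difference would then describe a diluted effect.

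**Working it through.** **Inputs.** From Sample size {14}: SD 15, correlation 0.7, alpha 0.05, power 0.8, effect 10, minimum 44, planned 60. From Trial design {8}: 1:1 allocation. From Objectives {7} and Statistical methods {20a}: visits at baseline, 3, 6 and 9 months.

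**Assumptions not in the article.** Two-sided test, compound symmetry, no dropout, and expected group differences of (0, 10, 10, 10).

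**1. Reproducing 44: group-by-time interaction, Hotelling-Lawley trace.**
- The noncentrality is (N/4) × [sum of squared deviations of the differences from their mean] / [SD² × (1 − correlation)].
- The mean difference is 7.5, so the sum is 7.5² + 3 × 2.5² = 75. The denominator is 225 × 0.3 = 67.5, and the ratio is 1.111.
- N = 42: noncentrality 11.67, power 0.784.
- N = 44: noncentrality 12.22, F with 3 and 40 df, power 0.807.
- N = 60: noncentrality 16.67, F with 3 and 56 df, power 0.927.

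The smallest even total reaching 80% is 44, which matches the article.

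**2. Declared test, baseline as a time level.**
- The expected fixed effect is (0 + 10 + 10 + 10)/4 = 7.5.
- The variance of a patient's four-visit mean is 225 × (1 + 3 × 0.7)/4 = 174.4, so the SD is 13.21.
- The standard error is 13.21 × √(4/N).
- N = 44: 7.5/3.98 = 1.88, power 0.453.
- N = 60: 7.5/3.41 = 2.20, power 0.581.
- N = 100: power 0.803 (98 gives 0.795).

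Simulating the main-effects model gave 0.448 and 0.583 at 44 and 60 with a random intercept, and 0.485 and 0.589 with an unstructured covariance. Over correlations from 0.5 to 0.9, power at 60 runs from 0.67 down to 0.51.

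**3. Main effect over 3, 6 and 9 months only, no baseline adjustment.**
- Effect 10; variance 225 × (1 + 2 × 0.7)/3 = 180; SD 13.42.
- N = 44: 10/4.05 = 2.47, power 0.676.
- N = 60: 10/3.46 = 2.89, power 0.810. At 58 it is just under 0.80, so 60 is the minimum.

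**4. Most generous main effect: a difference of 10 at all four visits, baseline included.** Power is 0.689 at 44, and 58 patients are needed.

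**5. Baseline as a covariate, treatment effect averaged over 3, 6 and 9 months.**
- Each post-baseline visit has covariance 0.7 × 225 = 157.5 with baseline. The residual variance is 180 − 157.5²/225 = 69.75, SD 8.35.
- N = 44: 10/2.52 = 3.97, power about 0.97.
- N = 60: 10/2.16 = 4.64, power above 0.99.

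| Test (two-sided 0.05) | Power at 44 | Power at 60 | N for 80% |
|---|---|---|---|
| Interaction, 4 visits | 0.81 | 0.93 | 44 |
| Main effect, baseline included | 0.45 | 0.58 | 100 |
| Main effect, 3, 6, 9 months, unadjusted | 0.68 | 0.81 | 60 |
| Main effect, constant 10 at 4 visits | 0.69 | 0.82 | 58 |
| Baseline-adjusted mean of 3, 6, 9 months | 0.97 | >0.99 | well below 44 |

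**The case against.** **The number 44 is not wrong in itself.** It reproduces, so there is no arithmetic error. This stands: the fault is a mismatch between the calculation and the test.

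**The interaction is inferred.** A reader might conclude that 44 can come only from the interaction with differences (0, 10, 10, 10). The article does not support that. The interaction with (0, 0, 0, 10), or over three visits with (0, 10, 10), also gives 44. So does a joint multivariate test with (0, 5, 10, 10), which is not an interaction test. The article states neither hypothesis nor profile. A one-sided main effect with a constant 10 comes out at 44 to 46, but no one-sided test is declared and the Hotelling-Lawley F test is not one-sided. None of these alternatives is the declared two-sided main effect.

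**The 58% is one reading.** It needs baseline to be an outcome level, which the article shows only through an example list, and it needs the assumed effect pattern. The objective names 3, 6 and 9 months, and on that reading 60 patients give 81%. This stands, and both figures should be reported. It does not rescue 44, which gives 68% on that reading.

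**Model detail belongs in the analysis plan.** Covariance structure and baseline handling often do, and an unseen plan may add an interaction or a baseline covariate. However, the article itself states both a powered sample size and a decision test, and these two do not fit each other.

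**Conclusion.** The point holds as a mismatch between two stated items. No two-sided treatment main effect tried under compound symmetry reaches 80% power at 44; the most favourable needs 58. As Statistical methods {20a} reads, with baseline a time level, power is about 45% at 44 and 58% at 60, and a true 10-point benefit is estimated as 7.5. With baseline left out, 60 evaluable patients are just enough, so the increase from 44 leaves no room for loss or for a less favourable SD or correlation. The Limitations section itself expects possible drop-out in the control group.

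These figures rest on the assumed differences (0, 10, 10, 10), compound symmetry and complete follow-up.

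A reader might infer that 60 patients are too few. The documents do not support that. The shortfall comes largely from averaging in the baseline visit and not adjusting for it. Under the same inputs, a baseline-adjusted comparison or the interaction is well powered at 60.

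**What to change.** Make the tested contrast and the powered contrast the same, and keep the objective at 3, 6 and 9 months. There are two ways:

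- **Baseline as covariate.** Remove baseline from the outcome levels in Statistical methods {20a}, adjust for it, and test the treatment effect averaged over 3, 6 and 9 months. Under the stated inputs, power is about 97% at 44 and over 99% at 60. The estimate is then on the 10-point scale and can be set against the clinically important difference.
- **Interaction.** Declare the group-by-time interaction as the primary test, with power 81% at 44 and 93% at 60. The clinical-importance comparison then needs its own named contrast, because an interaction over several visits is not a single effect.

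Then rewrite Sample size {14} to name the hypothesis, the assumed differences by visit and the covariance structure, with the power for that test. If the present main effect is kept, state its power: 58% at 60 with baseline included, 81% without, both before any loss.

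Moving to a single 9-month contrast is not needed and would change the primary comparison. The cost is minor rewriting of the two sections, with no change to the 60 patients. The change should be fixed before the outcome data are analysed.

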### Recruitment {15}

Patients will be recruited at the Mobility Clinic (which includes the outpatient clinic of the department of Orthopedics) of the University Medical Center Utrecht. We carry out over 250 surgical procedures for cartilage defects in our center annually.

## Assignment of interventions: allocation

### Sequence generation {16a}

Patients will be randomized into variable block sizes of two and four, stratified by defect size (< 4 or ≥ 4 cm^2^), using Castor EDC [26].

### Concealment mechanism {16b}

Allocation is not concealed and will be revealed to both the patient and the researcher upon randomization.

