### Trial design {8}

In this phase III randomized controlled clinical trial, IMPACT is compared to nonsurgical treatment. The patient allocation ratio is 1:1. Patients in the nonsurgical group are allowed to cross over to the treatment group after 9 months follow-up.

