### Implementation {16c}

After signing the informed consent forms, the researchers will use Castor EDC [26] to allocate the patient to one of the study arms. The study group will be revealed at the same time to both the patient and researcher.

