### Procedure for unblinding if needed {17b}

The trial design is open label, therefore there is no unblinding procedure.

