## Oversight and monitoring

### Composition of the coordinating center and trial steering committee {5d}

This is a monocenter study designed, performed and coordinated in the UMC Utrecht. Day to day support for the trial is provided by:

Principle investigator: takes supervision of the trial and medical responsibility of the patients.

Data manager: organizes data capture, safeguards quality and data.

Study coordinator: trial registration, coordinates study visits, annual safety reports.

Study physician: identifies potential recruits, takes informed consent, ensures follow-up according to protocol.

The study team meets biweekly. There is no trial steering committee or stakeholder and public involvement group.

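### Blocks of only two and four, in an open single-centre trial whose recruiting team sees every assignment, make about 72% of next allocations guessable; the statement that allocation is not concealed is a separate wording error

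*Protocol article*

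**What the plan says.** All references are to the protocol article.

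- **Sequence.** Sequence generation {16a}: "Patients will be randomized into variable block sizes of two and four, stratified by defect size", with the cut at 4 cm². Trial design {8}: "The patient allocation ratio is 1:1".
- **Concealment.** Concealment mechanism {16b}: "Allocation is not concealed and will be revealed to both the patient and the researcher upon randomization".
- **Who allocates, and when.** Implementation {16c}: "After signing the informed consent forms, the researchers will use Castor EDC", and then "The study group will be revealed at the same time to both the patient and researcher".
- **Who recruits.** The section on the coordinating center {5d} gives this role: "Study physician: identifies potential recruits, takes informed consent, ensures follow-up according to protocol". The same section describes one centre and a team that meets every two weeks.
- **Blinding.** The section on unblinding {17b}: "The trial design is open label, therefore there is no unblinding procedure".
- **Order at baseline.** Table 1 lists, for the baseline visit, consent, MRI, randomization and then the baseline patient-reported questionnaires.
- **Status.** Ten patients had been included by 15 May 2020, and recruitment was expected to end around August 2021. The article, which prints the block sizes, is dated 9 October 2020.

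**The concern.** In an open trial, past assignments are known to everyone involved. What protects against selective entry is that the next assignment stays unpredictable until the patient is committed. Small permuted blocks weaken this, because each block must return to balance within two or four patients. A team that tracks the running count per stratum can often tell which arm comes next, and the article describes no separation between recruiting and allocating.

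A recruiter with a good guess can affect when, or whether, a patient is brought to consent. The Limitations section expects patients to want immediate surgery, and the primary outcome, total KOOS, is self-reported without blinding. A difference in prognosis created at entry would be read as a treatment effect. Adjustment for baseline KOOS can remove only the part that KOOS measures. That baseline measurement is itself weaker if, as Table 1 lists it, the questionnaire is completed after the arm is known.

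**Working it through.** **Inputs.** Block sizes 2 and 4 and two strata (Sequence generation); ratio 1:1 (Trial design); 60 patients and a target effect of 10 KOOS points (Sample size). Assumption: the two sizes are equally likely. The plan states no figure for predictability, so there is none to reproduce.

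**Guessing rule.** Within a stratum, guess the arm that is behind; toss a coin when the arms are level.

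**Correct guesses per block.**
- Size 2 (AB or BA): 0.5 + 1 = 1.5 of 2, or 75.0%.
- Size 4: AABB gives 0.5 + 0 + 1 + 1 = 2.5; ABAB and ABBA each give 0.5 + 1 + 0.5 + 1 = 3; mirror images are the same. Mean (2.5 + 3 + 3)/3 = 2.833 of 4, or 70.8%.
- Equal mix: (1.5 + 2.833)/(2 + 4) = 72.2%. Any mix lies between 70.8% and 75.0%.

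**Assignments made when the arms are unequal.** Size 2: 1 per block. Size 4: (3 + 2 + 2)/3 = 2.333 per block. Equal mix: 3.333/6 = 55.6%. The guess is then right for 3 of 3.333, or 90%. The other 44.4% are coin tosses.

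**Lowest probability when the arms are unequal.** After the first patient of a new block, the other arm follows with probability 0.5 × 1 + 0.5 × 2/3 = 83.3%. So, with equal use of the sizes, every assignment made at imbalance has one arm above 80%. If a share *w* of blocks has size 2, this needs *w* + (1 − *w*) × 2/3 ≥ 0.8, that is *w* ≥ 0.4. With all blocks of size 4, the share at 80% or more is (1/3 + 1)/4 = 33%.

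**Certain assignments.** An imbalance of two can occur only halfway through a block of 4, so both remaining assignments are then known. This happens in one third of size-4 blocks: 2 × (1/3)/6 = 11.1%. If the size of the current block is known, the certain share is (1 + 1.333)/6 = 38.9%.

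**Simulation, 60 patients in two strata, 3000 trials, exact probability of the next assignment (sizes equally likely).**

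| Blocks | Correct guesses | One arm at ≥ 80% | Certain |
|---|---|---|---|
| 2, 4 | 71.7% | 54.6% | 10.5% |
| 4, 6 | 68.6% | 28% | 5.7% |
| 4, 6, 8 | 67.3% | 22% | 2.4% |

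The values for 2 and 4 fall slightly below the closed forms because the last block in a stratum may be incomplete. In the same setting, all blocks of 4 give 70.2% correct guesses and all blocks of 2 give 74.6%. A recruiter who ignores the strata and tracks only the total is right for about 66%.

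**Illustration of consequence (assumption, not in the documents).** Suppose entrants are *g* KOOS points better when IMPACT is guessed and *g* points worse when control is guessed. The expected difference between arms is 2 × 0.556 × (2 × 0.90 − 1) × *g* = 0.89*g*. For *g* = 1, 2.5 and 5 this is 0.9, 2.2 and 4.4 points, against a target of 10.

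**The case against.** A reader might infer from the concealment section that the allocation list lies open to recruiters. The documents do not support that. The arm appears upon randomization, in the electronic system, after signed consent, and to patient and researcher together; nothing says that the list can be seen beforehand. The sentence reads as concealment confused with blinding. None of the predictability figures depends on it, and they would be the same if the section said concealed.

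It can also be said that a guess is not knowledge: 44% of assignments are coin tosses and only about one in nine is certain. The treating surgeon judges eligibility before the consent meeting, at least two weeks of reflection follow, and controls may have IMPACT after 9 months, which weakens any motive to steer. Nothing shows that recruiters select patients; the Limitations section speaks of patients' preferences, impaired inclusion and drop-out. Larger blocks lower correct guesses by only about four points. Having someone outside recruitment trigger the allocation would not change this, because past assignments are still shown to the team.

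All of this stands as a limit on the claim. It does not remove the claim: approach and timing of consent remain with a team that knows the history, and the block-size calculation holds with a fully hidden list.

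**Conclusion.** The point holds as a risk. With blocks of two and four used equally often, about 72% of assignments can be guessed (50% is chance), about 55% have one arm at 80% probability or more, and about 11% are certain. The first figure is robust to the unstated mix, at about 70 to 75%. The second is not: it requires at least 40% of blocks to be of size two and falls to about one third if all are of size four. All the figures assume that the team knows the block sizes, which are published, and tracks two strata.

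Three stronger conclusions might be drawn and are not supported: that the list is open, that selection has occurred, and that no analysis could help. Adjustment for measured baseline differences is possible, but unmeasured differences remain, so selection could not be reliably repaired. The change is a cheap improvement to make for the remaining patients; the effect estimate is not shown to be invalid.

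**What to change.** 1. **Block sizes.** For patients still to be randomized, drop size two, use random blocks of 4, 6 and 8 within the same strata, and do not disclose the sizes to recruiting staff. The main gain is in assignments at 80% or more (about 55% to 22%) and certain ones (about 11% to 2%).
2. **Concealment section {16b}.** Replace the sentence with, for example: *The upcoming allocation is concealed. The electronic system releases it only after eligibility, consent and baseline questionnaires have been recorded. Once released, it is known to patient and researcher.* Align the order in Table 1. If the list can in fact be seen in advance, hide it.

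**Cost.** A system setting and a few lines of text. The maximum imbalance per stratum rises from 2 to 4 patients. Because recruitment has started, the change may need the amendment procedure described in the section on protocol amendments {25}. The assignments already made are unaffected.

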### Implementation {16c}

After signing the informed consent forms, the researchers will use Castor EDC [26] to allocate the patient to one of the study arms. The study group will be revealed at the same time to both the patient and researcher.

## Assignment of interventions: blinding

### Who will be blinded {17a}

Patients, researchers, and surgeons will not be blinded, since this is impossible due to the major difference between the two groups (surgical versus nonsurgical).

### Procedure for unblinding if needed {17b}

The trial design is open label, therefore there is no unblinding procedure.

## Data collection and management

### Plans for assessment and collection of outcomes {18a}

Data will be derived from electronic patient records and collected with an electronic Case Report Form (eCRF) using Castor EDC (Good Clinical Practice (GCP) Compliant) [26]. Patients will use an online survey (OnlinePROMS, InterActive Studios, Rosmalen, the Netherlands) to answer questionnaires. Laboratory tests are performed by the central diagnostic laboratory and MRIs will be made at the Department of Radiology of the UMC Utrecht. All radiographic data acquired during the study will be anonymized and saved in a study folder on our protected research server. Only the study team has access to this specific study folder. For the cost-effectiveness analysis, the resources required for the different procedures (i.e., IMPACT or nonsurgical treatment), as well as for the IMPACT product that is used (materials, operation theater, etc.), and the duration of the accompanying hospitalization will be derived from the electronic patient records. In addition, the results of the iMTA Medical Consumption Questionnaire will be used to collect data on resource use (including physiotherapist visits, home care, and medication use) and the results of the iMTA Productivity cost questionnaire will be used to collect data on productivity losses [27]. All resource use will be multiplied with cost prizes, which will be obtained from the Dutch Healthcare Authority [28], from UMC Utrecht hospital tariffs or from the Dutch manual for performing health economic evaluations [29], to calculate total societal costs. These costs will be combined with the QoL outcome measures (EQ-5D-5L), to calculate the incremental cost-effectiveness ratio of IMPACT compared to nonsurgical therapy in terms of cost per QALY over a 5-year time horizon.

